## 2.12 Publication of three papers in peer reviewed journals

A least three papers are expected to be published before completion of the PhD program in the peer review and international journal.

**Titles:**

1. Magnitude of metabolic and behavioral risk factors of type2 diabetes among urban street cooked food consumers from selected three districts in Dar es Salaam region
2. Knowledge and attitude on type2 diabetes among consumers and vendors of urban street cooked food from selected three districts in Dar es Salaam region
3. Assessment of socio-economic and cultural factors associated with adoption and compliance to the food plate model among consumers and vendors of urban street cooked food from selected three districts in Dar es Salaam region
4. Effectiveness of health prevention package in reducing metabolic risk factors for type2 diabetes consumers of urban street cooked food from selected three districts in Dar es Salaam region
5. A Bayesian model for predicting metabolic risk factors for type2 diabetes among consumers of urban street cooked food

2.13 Dissemination plan of research findings: Data emanating from this study will be presented and discussed with official from the Ministry of health and social welfare, Tanzania Diabetes Association, Afrique One ASPIRE, KCMUCo Academic forum and other stakeholders to identify feasibility of utilizing the findings to address type2 diabetes metabolic risk factors and nutrition related issues in Dar es Salaam and elsewhere. Reports will be produced and disseminated to the sponsors and the local health bodies and other stakeholders. At least three manuscripts manuscripts addressing different components in this project will be written and published in local and international peer reviewed journals.

Appendix A: <https://vizhub.healthdata.org/gbd-compare/>

[figure not shown]

[figure not shown]

Appendix B: **Data Collection tools**

**Effectiveness of prevention package and model for predicting metabolic risk factors of type2 diabetes among street cooked food consumers in Tanzania: A cluster randomized control trial**

**Section A: Information for Identification**

| **Q-Number** | **Question** | **Response** | **Code** |
| --- | --- | --- | --- |
| 1. | District: 1. Ilala 2. Kinondoni 3. Ubungo |  | Qn1 |
| 2. | Market place: |  | Qn2 |
| 3. | Category of cluster (market place): 1. Intervention 2. Control |  | Qn3 |
| 4. | Interviewer Names (Initials): |  | Qn4 |
| 5. | Date of an interview |  | Qn5 |
| 6. | Consent has been read and obtained: 1. Yes 2. No |  | Qn6 |
| 7. | Time of starting interview (24 hour clock) |  | Qn7 |
| 8. | Time of completing interview (24 hour clock) |  | Qn8 |
| 9. | Family Surname |  | Qn9 |
| 10. | First Name |  | Qn10 |
| 11. | Contact phone number where possible |  | Qn11 |
| 12. | Owner of the phone: 1. Office phone 2. Home  3. Neighbours’ 4. Others___________ |  | Qn12 |

**Section B: Step 1: Demographic Information**

| **Q-Number** | **Question** | **Response** | **Code** |
| --- | --- | --- | --- |
| 13. | Sex: 1. Male 2. Female |  | Qn13 |
| 14. | What is your date of birth? DD/MM/YYYY______________________  *Don't Know 77 77 7777* |  | Qn14 |
| 15. | How old are you? |  | Qn15 |
| 16. | In total, how many years have you spent at school or in full-time study (excluding pre-school)? ___________________________________ |  | Qn16 |
| 17. | Highest level of education attained: 1. None 2. Primary  3. Secondary 4. College |  | Qn17 |
| 18. | What is your **marital status**? 1. Never married 2. Married  3. Separated 4. Divorced  5. Widowed 6. Cohabiting |  | Qn18 |
| 19. | Which of the following best describes your **main work** status over the past 12 months?  1. Government employee 2. Non-government employee  3. Self-employed 4.Non Paid  5. Homemaker 6. Retired  7. Unemployed (able to work) 8. Unemployed (unable to work)  9. Refused |  | Qn19 |
| 20. | How many people older than 18 years, including yourself, live in your household?________________ |  | Qn20 |
| 21. | Taking **the past year**, can you tell me what the average earnings of the household have been?   1. Per day______________________________________ 2. Per week______________________________________ 3. Per month_____________________________________ 4. Per year_______________________________________ |  | Qn21a  Qn21b  Qn21c  Qn21d |

**Section D: Step 1: Attitudes towards living healthy life to prevent type2 diabetes**

| **Q-Number** | **Question** | **Response** | **Code** |
| --- | --- | --- | --- |
|  | **Statements** | 1.Strogly agree  2.Agree  3.Disagree  4.Strongly disagree |  |
| 22. | It is possible to prevent diabetes by dietary management |  | Qn22 |
| 23. | Family history of diabetes influences to follow disciplined life |  | Qn23 |
| 24. | Obesity increases the risk of diabetes |  | Qn24 |
| 25. | Regular exercise needs lots of effort |  | Qn25 |
| 26. | Everybody should be aware regarding prevention of diabetes with increasing age |  | Qn26 |
| 27. | If there is increased chance of getting diabetes e.g. having family history then there is nothing to do to prevent or delay occurrences of the disease. |  | Qn27 |
| 28. | If you try you can reduce the risk of diabetes |  | Qn28 |
| 29. | People who take steps to reduce the risk factors of diabetes, their possibility of occurring diabetes is less |  | Qn29 |
| 30. | You have little control on your health risk |  | Qn30 |
| 31. | If a person is rich and fat if the suddenly becomes thin and slender is a sign of running bankrupt |  | Qn31 |
| 32. | If somebody is fat has to maintain his/her body structure otherwise can be considered to be HIV positive |  | Qn32 |
| 33. | To become thin and slender is not good because people will consider one to be HIV positive |  | Qn33 |
| 34. | A glass of unsweeted juice is better than chewing the actual fruits |  | Qn34 |
| 35. | It is very difficult to yourself to avoind overfeeding if delicious foods are prently available |  | Qn35 |
| 36. | If salt is low teste low in foods it is better to add when you are eating in order to maintan the food teste |  | Qn36 |

**Section D: Step 1: Knowledge on type2 diabetes**

**Note: *This is a survey, not a test. Your answers will help identify which dietary advice people finding confusing. Therefore, if you do not know the answer, say `not sure/DK' rather than guess.***

| **Q-Number** | | **Question** | **Response** | **Code** |
| --- | --- | --- | --- | --- |
| *T2DM: Risk factors, symptoms, preventions strategies, complications Specific dietary related prevention strategies, nutritional values of foods and disease related with poor eating habits* | | | | |
| 37. | Have you had about diabetes? 1. Yes 2. No | |  | Qn37 |
| 38. | **If yes; mention at least five the risk factors of diabetes** | |  |  |
|  | 1. Age (40+ years) | |  | Qn38a |
|  | 1. Physical inactivity | |  | Qn38b |
|  | 1. Raised blood glucose | |  | Qn38c |
|  | 1. Raised cholesterol | |  | Qn38d |
|  | 1. Unhealthy eating | |  | Qn38e |
|  | 1. Family history of diabetes | |  | Qn38f |
|  | 1. Raised blood pressure | |  | Qn38g |
|  | 1. Alcohol consumption | |  | Qn38h |
|  | 1. Smoking | |  | Qn38i |
|  | 1. Excessive body weight | |  | Qn38j |
|  | 1. Gestational diabetes | |  | Qn38k |
|  | 1. Depression/stress | |  | Qn38l |
|  | 1. Others (specify)_______________________________ | |  | Qn38m |
| 39. | **Mention at least five symptoms of diabetes** | |  |  |
|  | 1. Extreme hunger | |  | Qn39a |
|  | 1. Frequent thirst | |  | Qn39b |
|  | 1. Frequent urination | |  | Qn39c |
|  | 1. Extreme weight loss | |  | Qn39d |
|  | 1. Blurred vision | |  | Qn39e |
|  | 1. Fatigue | |  | Qn39f |
|  | 1. Dry mouth | |  | Qn39g |
|  | 1. Dry or itchy skin | |  | Qn39h |
|  | 1. Poor wound healing | |  | Qn39i |
|  | 1. Extreme hunger | |  | Qn39j |
|  | 1. Frequent thirst | |  | Qn39k |
|  | 1. Others (specify)_______________________ | |  | Qn39l |
| 40. | **Mention at least five strategies for preventing type two diabetes** | | |  |
|  | 1. Control excessive body weight | |  | Qn40a |
|  | 1. Healthy eating habit | |  | Qn40b |
|  | 1. Control blood pressure | |  | Qn40c |
|  | 1. Healthy eating habit | |  | Qn40d |
|  | 1. Being physical active | |  | Qn40e |
|  | 1. Control blood glucose | |  | Qn40f |
|  | 1. Control blood cholesterol | |  | Qn40g |
|  | 1. Avoid excessive alcohol drinking | |  | Qn40h |
|  | 1. Avoid stress/depression | |  | Qn40i |
|  | 1. Quit smoking | |  | Qn40j |
|  | 1. Treat raised blood glucose during pregnancy | |  | Qn40k |
|  | 1. Others (specify)___________________________ | |  | Qn40l |
| 41. | **Mention at least five complications of type2 diabetes** | |  |  |
|  | 1. Amputation | |  | Qn41a |
|  | 1. Stroke | |  | Qn41b |
|  | 1. Kidney failure | |  | Qn41c |
|  | 1. Blindness | |  | Qn41d |
|  | 1. Impotence | |  | Qn41e |
|  | 1. Nerve damage | |  | Qn41f |
|  | 1. Heart attacks | |  | Qn41g |
|  | 1. Others (specify)_____________________ | |  | Qn41h |
| **Nutritional values** | | | | |
| 42. | What is the best composition of portion of carbohydrate, fruits, vegetables and proteins healthy food plate?  1) ¼ Carbohydrate, ¼ Protein, ½ Fruits and vegetables, Water/milk  2) DK  3) Others_______________ | |  | Qn42 |
| 43. | Do you think health experts recommend that people should be eating more, the same amount, or less of these foods? (Tick one box per food) | |  |  |
|  | **Food** | | **1.More**  **2.Same**  **3.Less**  **4.Not sure** |  |
|  | a) Vegetables | |  | Qn43a |
|  | b) Sugary foods | |  | Qn43b |
|  | c) Meat | |  | Qn43c |
|  | d) Starchy foods | |  | Qn43d |
|  | e) Fatty foods | |  | Qn43e |
|  | f) High fibre foods | |  | Qn43f |
|  | g) Fruit | |  | Qn43g |
|  | h) Salty foods | |  | Qn43h |
| 44. | How many servings of fruit and vegetables a day do you think experts are advising people to eat? (One serving could be, for example, an apple or a handful of chopped carrots)   1. Fruits _______________   b) Vegetable_______________ | |  | Qn44 |
| 45. | Saturated fats are mainly found in:(tick one)  1.Vegetable oils  2. Dairy products  3. Both (a) and  4. Not sure | |  | Qn45 |
| 46. | If a person wanted to reduce the amount of salt in their diet, which would be the best choice? (tick one)  1.Buy food with already added salts like sausages, manufacture beefs, chips crips etc  2. Add salt during cooking himself/herelf  3. Not sure | |  | Qn46 |
| 47. | Are you aware of the major non-communicable disease which is related to how much salt or sodium people eat?   1. Yes 2. No 3. Not sure | |  | Qn47 |
| 48 | If yes, which non-communicable disease do you think is related to salt?   1. High blood pressure 2. Not remember 3. Other______________________ | |  | Qn48 |
| 49. | Are you aware of any major non-communicable diseases that are related to a low intake of fruit and vegetables?   1. Yes 2. No 3. Not sure | |  | Qn49 |
| 50 | If yes, what non-communicable diseases do you think are related to a low intake of fruit and vegetables?   1. High blood pressure 2. Diabetes 3. Cancer 4. Not remember 5. Others________________ | |  | Qn50a  Qn50b  Qn50c  Qn50d  Qn50e |
| 51. | Are you aware of any major non-communicable diseases that are related to the amount of fat people eat? (Yes/No/DK) | |  | Qn51 |
| 52. | If yes, what non-communicable do you think are related to fat?   1. High blood pressure 2. Diabetes 3. Cancer 4. Not remember 5. Others________________ | |  | Qn52a  Qn52b  Qn52c  Qn52d  Qn52e |
| 53. | Are you aware of any major non-communicable diseases that are related to a low intake of fibre?   1. Yes 2. No 3. Not sure | |  | Qn53 |
| 54. | If yes, what diseases or health problems do you think are related to low intake of fibre?   1. High blood pressure 2. Diabetes 3. Cancer 4. Not remember 5. Others________________ | |  | Qn54a  Qn54b  Qn54c  Qn54d  Qn54e |
| 55. | Are you aware major non-communicable diseases that are related to excessive drinking of alcohol?   1. Yes 2. No 3. Not sure | |  | Qn55 |
| 56. | If yes, what non-communicable diseases that are related to excessive drinking of alcohol?   1. High blood pressure 2. Diabetes 3. Cancer 4. Not remember 5. Others________________ | |  | Qn56 |

**Section E1: Step 1: Behavioural Measurements –Tobacco Use**

***Now I am going to ask you some questions about various health behaviours. This includes things like smoking, drinking alcohol, eating fruits and vegetables and physical activity. Let's start with tobacco.***

| **Q-Number** | **Question** | **Response** | **Code** |
| --- | --- | --- | --- |
| 57. | Do you currently smoke any **tobacco products**, such as cigarettes, cigars or pipes? 1. Yes 2. No |  | Qn57 |
| 58. | Do you currently smoke tobacco products **daily**?  1. Yes 2. No |  | Qn58 |
| 59. | How old were you when you **first started** smoking daily?  Age (years)______________________DK: 77 |  | Qn59 |
| 60. | Do you remember how long ago it was? (Record one option only)   1. In Years_______________________ 2. OR In Months______________ 3. OR In Weeks_____________ 4. Don’t remember____________ |  | Qn60a  Qn60b  Qn60c  Qn60d |
| 61. | On average, **how many (number of sticks)** of the following do you smoke each day?*(RECORD FOR EACH TYPE, USE SHOWCARD)* *Don’t Know* |  |  |
|  | 1. Manufactured cigarettes__________ |  | Qn61a |
|  | 1. Hand-rolled cigarettes__________ |  | Qn61b |
|  | 1. Pipes full of tobacco__________ |  | Qn61c |
|  | 1. Cigars, cheroots, cigarillos__________ |  | Qn61d |
|  | 1. Others______________________________ |  | Qn61e |
| 62. | In the past, did you ever smoke daily?  1. Yes 2. No |  | Qn62 |
| 63. | How old were you when you stopped smoking daily? |  | Qn63 |
| 64. | How long ago did you stop smoking daily? (RECORD ONLY 1, NOT ALL 3)   1. In Years_______________________ 2. OR In Months______________ 3. OR In Weeks_____________ 4. Don’t remember____________ |  | Qn64a  Qn64b  Qn64c  Qn64d |
| 65. | Do you **currently use smokeless tobacco** products **daily?**  1. Yes 2. No |  | Qn65 |
| 66. | During the past 7 days, on how many days did someone **in your home** smoke when you were present? |  | Qn66 |
| 67. | During the past 7 days, on how many days did someone smoke in closed areas **in your workplace** (in the building, in a work area or a specific office) when you were present? |  | Qn67 |

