2.6.4 Effectiveness of intervention package in reducing type2 diabetes risk factors: At the end of an intervention the mean comparison using independent T-test of all metabolic risk factors for T2DM will be made between the control and intervention groups. For pre-post analysis, the study will apply Generalized Linear Mixed Models (GLMM) to accommodate fixed and random variables. Sensitivity analysis will be conducted to assess if variables which will be statistically significant by GLMM model, will be consistently significant using the Bayesian Modelling technique with Markov Chain Monte Carlo (MCMC). Post and baseline analysis will also employ both linear and logistic regression to assess the factors associated with both primary and secondary outcome of interest. The following are the metabolic risk factors which will be assessed: High Density Lipoprotein Cholesterol (HDL-C), Low Density Lipoprotein Cholesterol (LDL-C), Total Cholesterol (TC), and triglycerides Cholesterol (TG-C) Body mass index (BMI), Waist Hips Ratio (WHR) and Blood Pressure (BP) (4,5,22,23,47,49), these will be our primary outcome of interest. The study will also assess mean knowledge and attitude scores as our secondary outcomes, mean days of fruits/vegetable consumption per week, mean number of cigarettes smoked per week, drinks consumed per week and mean MET/week between the control and intervention sites. Frequency of alcohol consumption and smoking will be also compared between the control and intervention sites. Lastly, the study will also compare the proportion of quitting alcohol consumption and smoking tobacco products between the control and intervention sites.

2.6.5 Develop a model for predicting metabolic risk factors for type2 diabetes: After collecting the endline data then a model will be developed using Multivariate/Joint Bayesian techniques to assess socio-economic and behavirioal risk factors which influence each metabolic risk factors and those which influence these factors jointly. **Table 4** below shows the type of predictive/explanatory factors which will be modelled per each metabolic risk factor of T2DM(16).

Table 4 Dependent and independent variables

| **Dependent variables- Metabolic Risk factors of T2DM** | **Independent variables/confounders** |
| --- | --- |

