| 1. Body Mass Index or Waist Circumference 2. Fasting Blood Glucose 3. High Density Lipoprotein 4. Triglyceride 5. Systolic BP 6. Diastolic BP | **Socio-economic and demographic risks:**  Marital status, Education, Ethnicity, Employment status, Sex and Age  **Lifestyle behaviours**  Family history of diabetes  Smoking: Never/previously/currently; Frequency of smoking  **Physical activities**  Interview methods will be used in measuring:  Type, frequency and intensity, Work-related, communing and leisure physical activities  **Dietary pattern:**  Vegetables, Fruits, Spreads and oil, Table salt & Alcohol consumption  **Others factors:**  Mean number of health plate consumed per week,  Type2 diabetes knowledge of vendors and consumers |

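### The tobacco items ask about past smoking only if it was daily, so former occasional smokers cannot be told apart from never smokers, and the weekly cigarette count is ambiguous for current non-daily smokers

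*Protocol*

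**What the plan says.** Three parts of the protocol state what is needed on smoking.

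- **Table 4 (section 2.6.5)** lists the covariate for the prediction model as "Smoking: Never/previously/currently; Frequency of smoking".
- **Section 2.6.4** compares the "mean number of cigarettes smoked per week" between arms, and also the frequency of smoking and the proportion who quit.
- **Section 2.6.1, Smoking paragraph**, says that current smokers will be asked the age at which they began to smoke, separately from the age at which they began to smoke daily, and also how many cigarettes they smoke and how often.

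The form (Appendix B, Section E1) asks the following:

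- Qn57: "Do you currently smoke any tobacco products, such as cigarettes, cigars or pipes" (any frequency, yes/no).
- Qn58: "Do you currently smoke tobacco products daily" (yes/no).
- Qn59: "How old were you when you first started smoking daily". Qn60 asks how long ago that was.
- Qn61: "On average, how many (number of sticks) of the following do you smoke each day", by product.
- Qn62: "In the past, did you ever smoke daily". Qn63 and Qn64 ask when daily smoking stopped.

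The Swahili form also restricts Qn62 to daily smoking. Neither version asks whether the person ever smoked at all, or on how many days per week they smoke.

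**The concern.** The form does not collect what the plan's own variables need. Status in three levels requires knowing whether a present non-smoker ever smoked, and the form finds this out only for people who once smoked daily. Frequency of smoking is reduced to daily or not daily. A weekly count for someone who does not smoke every day needs either the number of smoking days or a direct weekly figure, and neither is asked.

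Two things are at stake. In the objective 5 model, the *never* reference group would absorb former occasional smokers, and *previously* would hold only former daily smokers, so the contrast between them would not mean what its labels say. In the arm comparison of cigarettes per week, non-daily smokers would contribute values on an unknown scale. An analysis plan can set coding rules, but it cannot recover answers that were never collected.

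**Working it through.** The protocol gives no figure on this point, so there is none to reproduce. The check has two steps.

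**Step 1. Answer pattern for each smoking history** (Qn57, Qn58 and Qn62 as worded in Section E1)

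| History | Qn57 current | Qn58 daily now | Qn62 past daily |
| --- | --- | --- | --- |
| Never smoked | No | – | No |
| Former, only ever occasional | No | – | No |
| Former daily | No | – | Yes |
| Current occasional, never daily | Yes | No | No |
| Current daily | Yes | Yes | – |

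The first two rows are identical. Qn59, Qn60, Qn63 and Qn64 concern only daily smoking, and Qn65 to Qn67 concern smokeless tobacco and other people's smoking, so nothing else separates the two groups. Current occasional smokers are identified correctly by Qn57.

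The English alcohol section of the same form has both missing elements: an item on ever drinking (Qn68) and a frequency scale (Qn70). The diet section asks days per week and servings per day (Qn76 to Qn79).

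**Step 2. Cigarettes per week from Qn61**

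Take a smoker of c sticks on each of k days per week. The true weekly count is k × c. The only conversion the form allows is 7 × Qn61.

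- If Qn61 is answered as an average over all days, it equals k × c / 7, and 7 × Qn61 = k × c, which is correct.
- If Qn61 is answered as the amount on a smoking day, it equals c, and 7 × Qn61 = 7c, which is too high by 7c / (k × c) = 7/k.

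| k (days per week) | 1 | 2 | 3 | 4 | 5 | 6 | 7 |
| --- | --- | --- | --- | --- | --- | --- | --- |
| 7/k | 7.0 | 3.5 | 2.33 | 1.75 | 1.4 | 1.17 | 1.0 |

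Example with assumed values c = 5 and k = 2. The true count is 2 × 5 = 10 per week. Read as an all-days average, Qn61 = 10/7 = 1.43 and 7 × 1.43 = 10. Read as a smoking-day amount, Qn61 = 5 and 7 × 5 = 35, which is 3.5 times the truth. The recorded data do not show which reading was used.

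**The case against.** The strongest reply is that Qn61 asks for an average per day. Someone who answers it as worded gives a rate, and seven times that rate is exact. The Swahili item also asks for an average per day. This stands. A reader might infer that cigarettes per week is wrong for everyone who does not smoke every day, but the wording does not support that. What remains is an ambiguity that cannot be checked afterwards.

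Three further inferences are tempting and also fail.

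- *A non-daily smoker's weekly count drops to zero.* The form prints no skip after Qn58 = No, so Qn61 is put to these people too. If it were left blank, the value would be missing. Nothing in the protocol turns a blank into 0.
- *A move from daily to occasional smoking goes unseen.* Qn58 changes from Yes to No and records it. Only the amount is uncertain.
- *An occasional smoker who quits during the trial becomes a never smoker.* Section 2.3 and the end-term form repeat the baseline items, so Qn57 = Yes at baseline and No at endline identifies a quitter. The quitting comparison in section 2.6.4 can be derived in the same way.

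It is also fair to say that no coding rule for *never* is written, and that derivations are commonly left to an analysis plan. So placing former occasional smokers under *never* is an inference. But for those who stopped before baseline, the items offer no basis for any other code.

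**Conclusion.** The point holds in limited form. The form and the plan's own variables disagree: former occasional smokers who stopped before baseline cannot be separated from never smokers. The initiation age and the smoking frequency described in section 2.6.1 are not obtained beyond the age at starting daily smoking and a daily yes/no. For current non-daily smokers the weekly count ranges from correct to 7/k times too high, depending on how Qn61 was understood.

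The number of participants affected cannot be estimated. Section 1.0 gives 15.9% tobacco users in a national survey. It gives no share of smokers who are non-daily and no share of former occasional smokers, and the survey is not of street-food consumers.

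The consequence is minor. The metabolic primary outcomes are not touched. The effect is on one covariate among many in the objective 5 model and on secondary behavioural comparisons. It is still worth correcting before baseline, because it cannot be repaired after data collection.

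**What to change.** 1. Reword Qn62 in both languages to ask whether the person ever smoked any tobacco product in the past, with a follow-up on whether that was daily. Keep Qn63 and Qn64 for those who smoked daily.
2. After Qn58 = No, ask either the number of days smoked per week together with the amount on such a day, or directly the number smoked per week.
3. State the derivation: 7 × Qn61 for daily smokers, and the new weekly item for the others.
4. For the endline model, code as *previously* anyone with Qn57 = Yes at baseline and No at endline. This uses data already planned and needs no change to the form.
5. Either add the general age-at-initiation item that section 2.6.1 describes, or remove it from that section.

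The cost is one reworded item and one or two added ones in two languages, about a minute of interview for smokers, and a small departure from the questionnaire on which the tool is based. If comparability with that source matters, Qn62 can stay as it is and the question on ever smoking can be placed before it.
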